#### Standard of care

All study participants are provided with HIV care and treatment that adhere to Tanzanian national guidelines. During the trial the ART initiation criteria within the Dar es Salaam HIV treatment program changed from CD4 T cell count <350 cells/μL or WHO HIV stage 3 or 4 disease to CD4 T cell count <500 cells/μL or WHO HIV stage 3 or 4 disease in January 2016. Per Tanzanian guidelines, zidovudine, lamivudine, and efavirenz are the choice first-line regimen with tenofovir, nevirapine, and stavudine as back-up drugs. The standard visit schedule for patients on ART is clinic visits at 2 weeks and 1 month post-initiation with monthly thereafter. Patients who are stable after 6 months of ART are eligible receive a 2-month supply of ART with a subsequent scheduled clinic visit at corresponding 2-month intervals. CD4 T cell counts are assessed at the ART eligibility visit and every 6 months after ART initiation. During the trial HIV viral load testing became available as standard of care with assessment every 6 months after ART initiation. Prophylaxis for opportunistic infections is provided in line with the Tanzanian HIV treatment guidelines. Participants receive co-trimoxazole prophylaxis if CD4 cell count is <200 cells/μL. All participants diagnosed with TB are treated according to the WHO-approved guidelines of the National Tuberculosis and Leprosy Program (NTLP) in Tanzania. All TB patients receive directly observed therapy (DOT) with a 6-month short course regimen consisting of a 2-month intensive phase of daily rifampicin/isoniazid/pyrazinamide/ethambutol (RHZE) combination tablets, followed by a 4-month continuation phase of daily rifampicin and isoniazid (RH) combination tablets. Sputa from smear-positive TB patients is collected and examined at 0, 2 and 5 months and at any other time if recurrence of TB is suspected. If the direct sputum smear is negative at the end of 2 months, the continuation phase is started and if a smear is still positive at 3 months the patient is checked for multi-drug resistance. Treatment failures and relapses are treated with an 8-month re-treatment regimen containing rifampicin throughout, with the intensive period with RHZE and streptomycin injection continuing for 3 months. Psychological and nutritional support is also provided as standard of care.

### Statistical analysis plan

An intent-to-treat analysis will be used as the primary analytic strategy for all analyses. The primary efficacy trial endpoints for this trial are (1) death and (2) incident pulmonary TB. The primary safety endpoint is hypercalcemia (albumin-adjusted calcium >2.6 mmol/L). We will use the use the log-rank test to test the differences in the incidence rates of death and pulmonary TB between the treatment arms, and use the Fisher’s exact test to test differences in proportion of participants with incident hypercalcemia.

The secondary endpoints for the study include: (a) post-randomization CD4 T cell count, (b) incidence of comorbidities and complications associated with HIV and/or ART, (c) post-randomization BMI, (d) incidence of wasting (BMI <18.5 kg/m^2^) and >10% weight loss from baseline, (e) post-randomization depression and anxiety scores as assessed by the Hopkins Symptom Checklist (HSCL), (f) post-randomization physical activity as measured by METs, (g) post-randomization bone health biomarker levels (PTH and ALP) and (h) post-randomization immunologic biomarker levels (IL-2, IL-12, IFN-γ, and cathelicidin). We will use linear mixed-effects models with a random intercept, a compound symmetric covariance structure, and robust standard errors to assess mean differences between baseline and post-randomization levels of CD4 T cell count, BMI, METs, 25(OH)D, PTH, ALP, IL-2, IL-12, IFN-γ, and cathelicidin by randomization group. Linear mixed-effects models will lead to robust inference for the fixed effects even if the covariance structure is misspecified. Linear mixed-effects models will also account for within-subject correlation, and accommodate varying number and timing of measurements per participant over time. We will use a generalized linear mixed model with random intercept, a compound symmetric covariance structure, and robust standard errors to assess differences in the incidence of comorbidities and complications associated with HIV and/or ART which are repeatable binomial events. The log-rank test will be used to assess differences in the incidence rates of wasting and >10% weight loss between the treatment arms.

We will also examine effect modification of any treatment effect by pre-defined baseline variables: 25(OH)D concentration, sex, age, BMI, CD4 T cell count, hemoglobin concentration, WHO HIV disease stage, pulmonary TB, receipt of isoniazid preventive therapy, ART regimen, and trial regimen compliance. To assess the statistical significance of each interaction, we will use the likelihood ratio test for risk-ratio homogeneity in the mortality, pulmonary TB, and hypercalcemia analyses and the score test in the linear mixed-effects and generalized linear mixed models for longitudinal secondary outcomes.

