### Primary and secondary objectives

The overall goal of ToV4 is to investigate a vitamin D_3_ as a simple and low-cost intervention to prolong and improve quality of life for HIV-infected women and men who are initiating ART. The two primary aims of the study are to determine the effect of a vitamin D_3_ supplementation regimen on the hazard of incident (1) mortality and (2) pulmonary TB as compared to a matching placebo regimen during the time period of enrollment at ART initiation to discharge at 1 year of follow-up. The secondary aims of the trial are to examine the effect of the vitamin D_3_ regimen on (a) post-randomization CD4 T cell count as mean difference in cells/μL, (b) incidence of comorbidities and complications associated with HIV and/or ART, (c) post-randomization body mass index (BMI) as mean difference in kg/m^2^, (d) incidence of wasting (BMI <18.5 kg/m^2^) and >10% weight loss from baseline, (e) post-randomization depression and anxiety as mean difference in Hopkins Symptom Checklist (HSCL) scores, (f) post-randomization physical activity as mean difference in metabolic equivalents (METs), (g) post-randomization bone health biomarkers [parathyroid hormone (PTH) and alkaline phosphatase (ALP)] as mean difference in concentrations (h) post-randomization immunologic biomarkers [interlukin-2 (IL-2), interlukin-12 (IL-12), interferon-gamma (IFN-γ), and the antimicrobial peptide cathelicidin] as mean difference in concentrations and (i) risk of hypercalcemia (albumin-adjusted calcium >2.6 mmol/L).

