#### Laboratory investigations

All participants have CD4 T cell counts assessed at or before the ToV4 screening/ART eligibility visit and then every 6 months after ART initiation. Hemoglobin is also measured at the ToV4 screening/ART eligibility visit. In order to examine the effect of the vitamin D_3_ regimen on bone health, we will measure PTH and ALP at baseline, 1, 6, and 12 months for a random sample of 800 individuals (20%). We will also assess the effect of vitamin D_3_ on host immune response through measurement of IL-2, IL-12, IFN-γ, and the antimicrobial peptide cathelicidin in 800 (20%) randomly selected individuals at baseline, 1, 6, and 12 months.

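### The claim that mixed models stay robust under a wrong covariance is made without condition, and the secondary contrast is worded differently from the objectives

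*Protocol article*

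**What the plan says.** In the Protocol article, Statistical analysis plan, the continuous secondary outcomes are CD4 count, BMI, METs, 25(OH)D, PTH, ALP, IL-2, IL-12, IFN-γ and cathelicidin. The model is stated as "We will use linear mixed-effects models with a random intercept, a compound symmetric covariance structure, and robust standard errors", and its purpose is "to assess mean differences between baseline and post-randomization levels of CD4 T cell count" and the other listed outcomes, by randomization group. Two further statements follow. One is the robustness claim, "Linear mixed-effects models will lead to robust inference for the fixed effects even if the covariance structure is misspecified". The other is that the models will "accommodate varying number and timing of measurements per participant over time", so incomplete follow-up is expected.

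Primary and secondary objectives defines the same endpoints differently, for example "post-randomization CD4 T cell count as mean difference in" cells/μL, with no reference to change from baseline.

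The repeated comorbidity endpoint has its own generalized linear mixed model, "to assess differences in the incidence of comorbidities and complications associated with HIV and/or ART which are repeatable binomial events".

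**The concern.** Two separate properties are at issue. Robust (sandwich) standard errors give a valid variance when the working covariance is wrong. They do not make the point estimate consistent. When participants with poorer earlier values are more likely to leave, a likelihood-based mixed model recovers the missing information through its covariance matrix. If that matrix is wrong, the visit means can be biased, and so can the arm contrast when dropout differs between arms. Compound symmetry imposes constant variance and constant correlation over a year of immune recovery on ART, which is a strong assumption for CD4.

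Second, baseline-to-post differences by arm read most naturally as change from baseline. That is not the quantity named in the objectives, and it can waste precision although a baseline value is planned for these outcomes. The matter is most relevant to the PTH/ALP and cytokine/cathelicidin samples, which have 800 participants each instead of 4000 (Laboratory investigations).

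**Working it through.** **The plan's own figures.** No power, SD or baseline-to-follow-up correlation is given for any longitudinal endpoint, so there is nothing to reproduce here. Table 2 concerns the primary endpoints only. It reproduces with 1800 per arm (for example 0.898 against the stated 90% for 10% mortality and RR 0.70) and does not bear on this point.

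**Inputs from the document.** One-year programme mortality is 13.1% (Background) and assumed loss to follow-up is 10% (Sample size). CD4 is measured at or before screening and then every 6 months. Biomarkers are measured at 0, 1, 6 and 12 months.

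**Inputs assumed.** All SDs, correlations, dropout models and effects below are assumptions.

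**Step 1: bias, CD4-like case.** Visits at 0, 6 and 12 months; SDs 110/160/190; correlations between 0.55 and 0.75; true 12-month effect 25 cells; dropout depending on earlier CD4. Where several sets of assumptions were tried, the range is shown.

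| Dropout | Compound symmetry | Shortfall from 25 | In 12-month SDs (÷190) |
|---|---|---|---|
| Same model in both arms | 24.2 to 25.0 | 0 to 0.8 (0 to 3%) | 0.000 to 0.004 |
| Only the rate differs (about 24% vs 18%) | 22.7 | 2.3 (9%) | 0.012 |
| Dependence on CD4 differs by arm | 18.9 to 16.5 | 6.1 to 8.5 (24% to 34%) | 0.032 to 0.045 |

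Unstructured covariance gave about 25 in each situation.

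**Step 2: bias, standardised case.** Visits at 0, 1, 6 and 12 months; SD about 1; true effect 0.20 or 0; compound symmetry fitted.
- Missing completely at random: no detectable bias, whatever the true covariance.
- Same dropout mechanism in both arms: at most 0.002 SD.
- Dependence differing by arm: +0.011 SD if the truth is AR(1), and −0.012 to −0.019 SD if it is a random slope.
- Only the rate differing, random-slope truth: 0.1927 against 0.20, that is −0.007 (Monte Carlo error 0.0024).
- True compound symmetry: none detectable.

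Both the size and the sign of the bias therefore depend on the true covariance and on how dropout differs by arm.

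**Step 3: precision of a change contrast.** Take one follow-up visit, baseline SD s0, follow-up SD s1 and correlation ρ:
- change variance = s0² + s1² − 2ρ·s0·s1
- baseline-adjusted variance = s1²(1 − ρ²)
- the difference is (s0 − ρ·s1)², which is never negative.

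With equal variances, change/adjusted = 2/(1 + ρ). This is 1.54, 1.33 and 1.18 at ρ = 0.3, 0.5 and 0.7. For 800 participants the effective number is 800(1 + ρ)/2 = 520, 600 and 680.

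With the assumed CD4 SDs at 12 months (110 and 190):
- ρ = 0.55: change 25,210; adjusted 25,179.75; adjusted/change 0.999
- ρ = 0.65: 21,030; 20,847.75; 0.991
- ρ = 0.75: 16,850; 15,793.75; 0.937

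At 6 months (110 and 160) the adjusted/change ratios are 0.974, 0.998 and 0.991. Adjustment thus saves about 0 to 6% for CD4 if its variance grows in this way, because ρ·s1 then lies close to s0 (0.55 × 190 = 104.5 against 110).

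**The case against.** The best defence is that the sentence just before the claim specifies robust standard errors. With them, inference under a wrong covariance is valid for complete data or data missing completely at random. A reader might infer that the robustness claim is simply false. The document does not support that: the claim is true under a condition it leaves out. This part of the defence stands.

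A reader might also object to a random intercept combined with compound symmetry. A random intercept with independent residuals implies compound symmetry, so the two phrases can name one structure. Nothing says that a second compound-symmetric matrix is added, and the wording causes neither bias nor loss of precision.

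On the contrast, the article does not give the fixed effects. A model with baseline as a response and a common baseline mean also fits the text and loses nothing, and that detail may sit in a full analysis plan. This is fair. What remains is that the two sections word the quantity differently.

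It would also be too broad to say that every longitudinal endpoint is affected. The comorbidity model has no baseline contrast, and the HSCL scores are not in the list of outcomes for the linear mixed model.

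Finally, the 24% to 34% shortfall looks large partly because a 25-cell effect was assumed; in SD units it is 0.032 to 0.045. The defence does not remove the central point: the claim is stated without condition, in a plan that expects incomplete follow-up and tests an intervention meant to change who dies or falls ill.

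**Conclusion.** The point holds in limited form. The robustness claim needs a missing-data condition. If dropout depends on earlier observed values and differs by arm, a compound-symmetric fit can bias the arm contrast. In the cases tried, the bias ran from almost none to about a third of an assumed 25-cell CD4 effect, or roughly 0.00 to 0.045 SD. With identical dropout models in both arms it was negligible.

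The precision cost applies only if the contrast really is change from baseline with arm baselines left free. It is then 18% to 54% in variance for ρ from 0.7 to 0.3 with equal variances, and close to nil for CD4 under the assumed growth in variance. None of these SDs, correlations or dropout models comes from the document.

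A reader might infer from the expected mortality that a better covariance would protect against bias from death. It would not. CD4 after death is undefined, and loss that depends on unobserved values is a separate problem; no covariance choice solves either. Only secondary continuous endpoints are concerned. The log-rank tests for death and pulmonary TB and the Fisher test for hypercalcemia are untouched.

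**What to change.** 1. Delete the robustness sentence, or limit it to complete data or data missing completely at random and attribute it to the robust standard errors.
2. For the continuous outcomes at three or four fixed visits (CD4, METs, 25(OH)D, PTH, ALP, the cytokines and cathelicidin), fit visit as a factor with unstructured covariance, and either constrain the baseline mean to be common to both arms or include baseline as a covariate.
3. Report the arm difference at each post-randomization visit, and reword the analysis section to match the objectives.
4. State that this model does not address truncation by death or loss that depends on unobserved values.

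BMI is measured at every clinic visit, so an unstructured matrix is not the natural choice there and item 2 does not cover it.

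The cost is wording, plus visit windows to assign measurements to scheduled visits. Covariance parameters rise from 2 to 6 with three visits (3 × 4/2) or 10 with four (4 × 5/2), which is trivial with 800 to 4000 participants. No extra data are needed.

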#### Hypercalcemia assessment

All participants have serum calcium and albumin assessed at baseline, 1, 6 and 12 months. Serum calcium and albumin concentrations are assessed with the Roche Cobas Integra 400 Plus (Roche Diagnostics, Basel, Switzerland). Albumin-adjusted serum calcium concentrations are then calculated using the following equation: calcium (mg/dL) = total calcium (mg/dL) + 0.8 × [4 − albumin (g/dL)] [47]. Any participants with above the normal physiologic range of albumin-adjusted calcium (>2.6 mmol/L) are diagnosed with hypercalcemia, discontinue their trial regimen for the duration of the trial and are given appropriate clinical management. Individuals with hypercalcemia continue to be followed up until discharge of the trial and resolution of hypercalcemia. In addition participants are monitored at all clinic visits by study physicians for symptoms of hypercalcemia including: nausea, vomiting, excessive thirst, anorexia, symptoms of kidney stones, and confusion. If any of these symptoms are reported and there is no other suspected cause, study clinicians order calcium and albumin testing. At this point participants with suspected hypercalcemia stop their randomized treatment regimen until calcium testing results are returned. If albumin-adjusted calcium levels are normal for hypercalcemia suspects, the patient is allowed to re-start the regimen under discretion of study physicians. Hypercalcemia suspects with albumin-adjusted calcium >2.6 mmol/L discontinue their trial regimen for duration of the trial and are given appropriate clinical management.

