#### Compliance assessment

Any trial requires a high degree of compliance with experimental regimens as non-compliance can bias results and decrease the statistical power of a study. The best way to ensure full compliance is to observe each participant ingesting treatment. In ToV4 research nurses directly monitor subjects taking the weekly trial supplements (randomization, week 1, week 2, week 3), but this type of monitoring is not practical for the subsequent daily supplements taken in the home (week 4 to month 12). In order to promote adherence during the daily regimen period, all participants are encouraged to use the daily supplements at the same time every day, to put the bottle in a visible place, and identify an adherence assistant who would remind her/him to take the supplement. Compliance with the daily ToV4 supplements will be assessed three ways: (a) direct questioning about use of the supplements in the previous 24 hours and 2 weeks, (b) pill count from returned daily regimen bottles, and (c) biochemical assessment of 25(OH)D in a subset of participants longitudinally at randomization, 1, 6, and 12 months.

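### Trial regimen compliance is listed as a baseline effect modifier but is measured after randomization, so its strata are not randomized comparisons, and for hypercalcemia they are circular

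*Protocol article*

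**What the plan says.** The Statistical analysis plan section of the protocol article announces "effect modification of any treatment effect by pre-defined baseline variables". It names eleven variables, the last three being "receipt of isoniazid preventive therapy, ART regimen, and trial regimen compliance". Each interaction is to be tested in the same way: by a "likelihood ratio test for risk-ratio homogeneity in the mortality, pulmonary TB, and hypercalcemia analyses", and by a score test in the mixed models for the longitudinal secondary outcomes. Compliance gets no separate treatment or caveat.

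The Compliance assessment section describes how compliance is observed. Nurses watch the weekly doses at randomization and at weeks 1, 2 and 3. For the "subsequent daily supplements taken in the home (week 4 to month 12") there are three measures: questioning about recent use, "pill count from returned daily regimen bottles", and serial 25(OH)D in a subset of participants.

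The Hypercalcemia assessment section says that participants with raised albumin-adjusted calcium "discontinue their trial regimen for the duration of the trial". Hypercalcemia is also the primary safety endpoint.

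**The concern.** A baseline variable is fixed before allocation, so each of its levels contains a small randomized trial. Compliance is fixed afterwards. If the arm affects who complies, the compliers in one arm are a different kind of patient from the compliers in the other, and the contrast between them mixes any treatment effect with selection. An interaction test across such strata can reject when the treatment does nothing. Equally, both stratum estimates can drift in the same direction while the interaction test stays silent.

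The trial is meant to give causal evidence on mortality and pulmonary TB. A pre-specified result that vitamin D works in compliers, presented in the same table as sex, age and CD4 count, would be read as a randomized subgroup finding. That temptation is strongest if the main comparison is null.

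**Working it through.** **1. The sections set side by side.** The Statistical analysis plan section calls all eleven modifiers baseline. The Compliance assessment section contains no compliance measure taken before randomization: the earliest is the observed dose at the end of the randomization visit, and the rest run to month 12. No other section defines a baseline version or an estimator suited to a post-randomization variable. The label is therefore wrong as written.

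**2. Routes from arm to compliance in the article.**
- Hypercalcemia ends the regimen. If vitamin D raises its incidence, the active arm acquires extra non-compliers by rule.
- Follow-up 25(OH)D is one compliance measure, and the active capsules are expected to raise it by about 20 ng/mL. It is measured only in a subset, so it cannot classify all 4000 participants.

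**3. Hypercalcemia endpoint.** Calcium is tested in everyone at baseline, 1, 6 and 12 months, and on symptoms. A case found at month 1 or 6 stops capsules for the remaining months and then scores low on use. Cases are thereby sorted into the non-compliant stratum by the event being analysed, in either arm. This follows from the text without any assumed number, unless the instructed stop is left out of the compliance measure, which the article does not say.

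**4. Check of the design inputs.** The article gives no figure for the effect-modification analysis. As a check on the sample-size inputs, take 1,800 per arm (4000/2 × 0.90), placebo mortality p1 = 0.125, RR 0.75 (p2 = 0.09375) and two-sided 5%:
- SE under the null = √(2 × 0.109375 × 0.890625/1800) = 0.01040
- SE under the alternative = √((0.125 × 0.875 + 0.09375 × 0.90625)/1800) = 0.01039
- Power = Φ((0.03125 − 1.96 × 0.01040)/0.01039) = 85.2%, against 85% stated.

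The compliance point changes no power figure.

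**5. Illustration A, with all inputs assumed and no true effect.** In both arms 20% are poor compliers with 25% mortality and 80% are good compliers with 7.5% mortality. Overall mortality is 0.20 × 0.25 + 0.80 × 0.075 = 11%. Let a fraction m of the vitamin D arm, with good-complier risk, move from good to poor. Poor-complier mortality in that arm is then (0.05 + 0.075m)/(0.20 + m), to be divided by 0.25 for the RR. The good-complier RR stays at 1.00. The last column is the rejection rate of a two-sided 5% Wald test comparing the two log-RRs, with 1,800 per arm.

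| m | Poor-complier mortality, vitamin D | RR | Interaction z | False rejection |
|---|---|---|---|---|
| 2% | 0.0515/0.22 = 0.234 | 0.94 | 0.36 | about 6.5% |
| 5% | 0.05375/0.25 = 0.215 | 0.86 | 0.82 | about 13% |
| 10% | 0.0575/0.30 = 0.192 | 0.77 | 1.43 | about 30% |

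**6. Illustration B, a simulation on assumed parameters with no true effect.** Frailty u is standard normal. The log-odds of death are −2.3 + u, giving mortality of about 12.4%. The log-odds of compliance are 1.4 − u in the placebo arm and 1.4 − u − s·u − l in the vitamin D arm. The intent-to-treat RR is about 1.00 throughout. False rejection is from 2,000 simulated trials of 3,600 participants.

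| Effect of arm on compliance | RR, compliers | RR, non-compliers | False rejection |
|---|---|---|---|
| None | 1.00 | 1.01 | 5% |
| s = 0.25 | 0.95 | 1.05 | 9% |
| s = 0.5 | 0.90 | 1.09 | 20% |
| s = 1.0 | 0.82 | 1.13 | 44% |
| l = 1.0 (compliance 76% to 58%) | 0.87 | 0.88 | 5% |

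The first row shows that the bias disappears when arm does not affect compliance. The last row shows that both strata can be biased without the interaction test noticing.

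**The case against.** The best defence has four parts.

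- **Scope.** Intent-to-treat is the primary strategy, with log-rank tests for death and pulmonary TB and Fisher's exact test for hypercalcemia. Compliance is one of eleven modifiers in a secondary analysis. This stands: no primary estimate, test or power figure changes, and a reader who infers that the main results are compromised goes beyond the document.
- **Likelihood of bias.** The capsules look and taste alike and participants and staff are blinded, so arm may have little influence on capsule-taking. The article also expects very low side-effect risk from the daily dose, which makes the larger shifts in Illustration A less plausible for hypercalcemia stops alone. This stands as a limit on size. It does not make compliance a baseline variable or remove the stopping rule.
- **Early deaths.** A reader might infer that everyone who dies before week 4 drops out of the compliance analysis. The article does not support that as a certainty. Doses at randomization and weeks 1 to 3 are observed, so early deaths can have a compliance value, and the text does not say which measure defines the strata. It places most deaths in the first months, not before week 4.
- **25(OH)D.** A reader might also infer that the strata would simply reproduce the arms, because vitamin D raises 25(OH)D. As the marker is measured only in a subset, that is a weak argument for mortality and TB.

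The objection narrows the consequences but does not rescue the wording.

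**Conclusion.** The plan is wrong as written on this item: a variable measured after randomization is called baseline and given the same interaction test as true baseline covariates, for mortality, pulmonary TB, hypercalcemia and the longitudinal outcomes. The resulting strata are not protected by randomization. For hypercalcemia the analysis is circular, because the event ends use of the regimen.

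The effect is confined to a secondary analysis. Bias in the mortality and TB strata is conditional on arm affecting compliance, and its size cannot be derived from the article. The RRs of 0.94, 0.86 and 0.77 and the false-rejection rates show only what can happen under the assumed inputs. Illustration A leaves good compliers at 1.00, so it does not by itself show a spurious benefit in compliers. Illustration B does, but only if frail patients comply less on the active arm (s above 0) or the active arm lowers compliance across the board (l above 0).

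**What to change.** Delete trial regimen compliance from the list of baseline effect modifiers, leaving ten variables, and do not run the compliance interaction for hypercalcemia.

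If an adherence analysis is wanted, there are two acceptable forms:
- Keep it outside the effect-modification list, labelled exploratory and non-randomized. A landmark analysis or one with time-varying adherence belongs here and must be called observational, since neither preserves the randomized comparison.
- Estimate a complier-average causal effect with randomized arm as the instrument. State that the exclusion restriction is strained, because participants who do not take the daily capsules may still have received the observed weekly doses.

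The change is one line of text. The price is the loss of one naive subgroup table, or its replacement by a somewhat more complex exploratory analysis. Recruitment was still open at publication and the allocation codes are held by non-study statisticians until the primary analyses are complete, or earlier if the DSMB asks for them, so the wording could be corrected before unblinding.
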